**Table 4: Dose delay and adjustment due to general toxicities**

| Toxicity / NCI-CTCAE grade                                                   | Actions to be taken                                                                                                                                                                                                                               |
|------------------------------------------------------------------------------|---------------------------------------------------------------------------------------------------------------------------------------------------------------------------------------------------------------------------------------------------|
| Administration related reaction                                       | Please refer to 4.3.4.                                                                                                                                                                                                                            |
| Other Toxicities                                                      |                                                                                                                                                                                                                                                   |
| Grade 1                                                                      | 1. Monitor as clinically required.
2. No dose adjustment is required.                                                                                                                                                                          |
| Grade 2 or 3, clinically significant but uncontrollable with supportive care | 1. Interrupt HQP1351 administration for up to 2 weeks (14 days) until toxicity resolves to Grade $\leq 1$ .
2. Resume HQP1351 administration at a reduced dose level and monitor as needed.
3. A maximum of two dose reductions is allowed. |

[figure not shown]

| Toxicity / NCI-CTCAE grade | Actions to be taken                                                                                                                 |
|----------------------------|-------------------------------------------------------------------------------------------------------------------------------------|
|                            | 4. If Grade 2 or 3 toxicity recurs after two dose reductions, stop HQP1351 administration, and follow up according to the protocol. |
| Grade 4                    | Stop HQP1351 administration, and follow up according to the protocol.                                                               |

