#### **4.3.2 Dose adjustment**

AEs that occur during this study will be graded according to National Cancer Institute-Common Terminology Criteria for Adverse Events (NCI-CTCAE) (v4.03). According to the correlation of AEs with the study drug and grade, the investigator will take different actions with the study drug, including maintaining the original treatment regimen, withholding dosing, reducing the dose, and terminating the treatment. Up to twice dose reductions are allowed, each to the next lower dose already explored. Any adult subject requiring a reduction of HQP1351 dose below 30 mg QOD should permanently discontinue the study treatment. The study drug can be resumed when the study drug-related toxicities resolve to grade 1 or below.

Dose adjustment may not be performed for grade 1/2 toxicities related to the study drug that can be treated by supportive treatment or don't influence normal daily activities of subjects, unless QTc prolongation, clinically significant pancreatitis, or other clinical conditions that affect subject's safety at the investigator's discretion. For intolerable (symptomatic or influencing subject's normal daily activities) or persistent (unable to be handled with the best supportive care and recovered to grade 1 or baseline after up to 2-week of drug withdrawal) grade 1/2 toxicities related to the investigational product, whether to make dose adjustment will be determined by discussion between the PI and the sponsor.

If a subject experiences grade 3 or 4 investigational drug-related toxicities, the investigational drug should be interrupted immediately. A maximum of 2 weeks (14 days) of drug interruption is permitted to resolve toxicities to Grade 1 or below, or baseline level. The investigational drug can be resumed when the toxicities resolve to Grade 1 or below, or baseline level. Each subject may undergo a maximum of twice dose reductions throughout the study period, and dose increases are generally no longer allowed after dose reductions. Please refer to Table 2-4 for guidance on dose adjustment for study drug-related toxicity.

[figure not shown]**Table 2: Dose delay and adjustment due to hematologic toxicities**

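### After a drug-related Grade 4 toxicity, the section 4.3.2 text permits resumption, but five of the seven graded Grade 4 rows in Tables 2 to 4 require stopping

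*Protocol*

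**What the plan says.** The text of section 4.3.2 sets one rule for the two highest non-fatal grades: "If a subject experiences grade 3 or 4 investigational drug-related toxicities, the investigational drug should be interrupted immediately". It allows at most 14 days of interruption and continues: "The investigational drug can be resumed when the toxicities resolve to Grade 1 or below, or baseline level". Earlier in the same section a general sentence says much the same: "The study drug can be resumed when the study drug-related toxicities resolve to grade 1 or below". Neither resumption sentence is limited by type of toxicity. The paragraph ends: "Please refer to Table 2-4 for guidance on dose adjustment for study drug-related toxicity".

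The tables are stricter at Grade 4. In Table 4, the Grade 4 row for other toxicities tells the site to "stop HQP1351 administration, and follow up according to the protocol". Table 2 says stop for Grade 4 febrile neutropenia and Grade 4 anemia. Table 3 says stop for Grade 4 bilirubin and Grade 4 AST/ALT. Only the Grade 4 platelet and neutrophil rows of Table 2 provide for a restart.

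On lower grades, for intolerable or persistent drug-related Grade 1 or 2 toxicity the text says that "whether to make dose adjustment will be determined by discussion between the PI and the sponsor". Table 4, for clinically significant Grade 2 or 3 toxicity that supportive care cannot control, directs an interruption of up to 14 days and then a restart at a reduced dose.

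**The concern.** Whether a subject may receive the drug again after a Grade 4 drug-related toxicity is a patient-safety rule, and the protocol answers it in two ways. Table 2 itself describes Grade 4 febrile neutropenia and Grade 4 anemia as life-threatening, and section 9.2.5 describes Grade 4 events generally in those terms.

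The data are affected as well. Safety and tolerability are the primary objective and endpoint. Section 10.4.3 lists adverse events leading to discontinuation, and section 4.4 bases the recommended Phase II dose partly on tolerability. In a multicentre study, the same event could be recorded as an interruption at one site and as a discontinuation at another, depending on which part of section 4.3.2 was followed.

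**Working it through.** No sample size, power or error rate is involved. The check sets the rules side by side.

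**1. A test case.** Take a drug-related Grade 4 event under other toxicities that recovers to Grade 1 on day 10 of interruption.
- Text of 4.3.2: the 14-day limit is met and recovery is to Grade 1, so the drug can be resumed.
- Table 4, Grade 4 row: the drug is stopped, and no resumption step follows.

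**2. Whether stop could mean interrupt.** It cannot. The Grade 4 platelet row in Table 2 uses both words for different actions: interrupt first, restart at a reduced dose, and stop only if Grade 4 recurs. The 4.3.2 text also lists withholding doses and terminating treatment as separate actions.

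**3. Count of the graded Grade 4 rows.**

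| Table | Toxicity, Grade 4 | Action | Recovery threshold for restart |
|---|---|---|---|
| 2 | Platelets | Restart at reduced dose; stop on recurrence | Grade 1 or below |
| 2 | Neutrophils | Restart at reduced dose; at most two reductions | At least 1.0 × 10⁹/L |
| 2 | Febrile neutropenia | Stop | None |
| 2 | Anemia | Stop | None |
| 3 | Total bilirubin | Stop | None |
| 3 | AST/ALT | Stop | None |
| 4 | Other toxicities | Stop | None |

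Stop: 5 of 7. Restart: 2 of 7. Table 3's combined AST/ALT-with-bilirubin entry has no grade and is not counted; it also says stop.

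Only the platelet row (1 of 7) uses the text's threshold of Grade 1 or below. Table 2 defines Grade 2 neutropenia as 1.0 to below 1.5 × 10⁹/L, so the neutrophil row allows a restart while the subject is still at Grade 2.

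**4. Precedence.** The text refers to Tables 2 to 4 as guidance. Nothing in 4.3.1, 4.3.2 or the tables says that a table row overrides the text, or the reverse.

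**5. Section 4.2.** Intolerable toxicity leads to permanent discontinuation unless the investigator weighs risk and benefit, discusses the case with the sponsor, and continuing is in the subject's best interest. That is a case-by-case exception. The resumption sentences in 4.3.2 require no such discussion, so 4.2 does not reconcile them with the stop rows.

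**6. Grade 2 (secondary).** The two triggers are worded differently. The text's intolerable class means symptomatic or affecting daily activities. Its persistent class already assumes up to two weeks off drug without recovery. Table 4's trigger is clinically significant Grade 2 that supportive care cannot control, and its dose reduction follows recovery. The clear overlap is intolerable, uncontrolled Grade 2 that recovers within 14 days: the text leaves adjustment to discussion, while Table 4 reduces the dose. At 40 mg the reduction is to 30 mg, (40 − 30)/40 = 25%. At 30 mg a mandatory reduction ends treatment: "Any adult subject requiring a reduction of HQP1351 dose below 30 mg QOD should permanently discontinue the study treatment".

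**The case against.** The best defence is that the text is the general rule and the tables are the specific one. Section 4.3.2 opens by saying that the action depends on causality and grade, and it names termination as one option. The Grade 3 or 4 paragraph gives no restart dose and sends the reader to the tables. A site that wants to resume after a Grade 4 other toxicity would therefore open Table 4 and find stop. On this view the permission to resume only states a recovery condition, and what is missing is a sentence on precedence. Section 4.2 adds a further safeguard against careless re-exposure.

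Much of this stands as a forecast of behaviour: most sites would probably follow the table. It does not remove the contradiction. The resumption sentence names Grade 4 explicitly and excepts no toxicity, the tables are labelled guidance, and the permission is contradicted in five of seven rows.

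The defence is stronger on Grade 2. A reader might infer that the text and Table 4 conflict across Grade 2 generally. They do not. Both leave the dose alone when supportive care controls the event, and the remaining overlap is narrow. A reader might also take every stop row to mean a permanent stop without exception. Section 4.2 does not support that, because it allows continuation after a documented discussion with the sponsor.

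**Conclusion.** The Grade 4 rule is inconsistent as written and should be corrected. Its size is five of seven graded Grade 4 rows in which the tables say stop and the text permits resumption. In one of the two restart rows, neutrophils, the recovery threshold also differs from the text.

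The conclusion rests on the literal wording and on the absence of any precedence statement. The hypertension guidance in section 4.3.5 is a figure that is not available, so nothing is concluded about it.

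The documents give no frequency for drug-related Grade 4 events or for any rechallenge after them. A reader might infer that subjects have been re-exposed, or might use the enrolment by dose in section 1.5 to estimate how many face the 30 mg floor. Neither inference is supported. The first has no data behind it. The second would use a cumulative count from January 2021, and non-randomized adults now receive 40 mg.

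The Grade 2 ambiguity is real but minor.

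**What to change.** In the text of section 4.3.2:
- Limit the Grade 3 or 4 resumption sentence to Grade 3 toxicities and to Grade 4 platelet or neutrophil decreases, the latter at the recovery threshold and dose in Table 2. Apply the same Grade 4 limit to the earlier general resumption sentence, which also serves interruptions at lower grades.
- State that all other drug-related Grade 4 toxicities stop HQP1351 as in Tables 2 to 4, subject only to the documented investigator-sponsor best-interest exception in section 4.2.

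As a minor addition, state whether Table 4's dose reduction is mandatory for intolerable Grade 2 toxicity that supportive care cannot control, or is left to the discussion between the principal investigator and the sponsor.

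Targeted wording is safer than a blanket sentence that the tables govern. Such a sentence could let Table 4's Grade 1 row, which requires no dose adjustment, displace the exception in the text that begins "unless QTc prolongation, clinically significant pancreatitis, or other clinical conditions".

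The cost is small: an amendment to wording, with no new data or visits. The downside is that some past dosing decisions made under one reading may be reclassified as protocol deviations.

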#### 4.3.3 Principles for management of serum troponin increased

If a subject develops serum troponin increased during treatment with HQP1351, the following measures are recommended:

- To evaluate cardiac function of the subject and recommend to perform the following examinations:
  - Serial serum troponin test
  - Echocardiogram
- TEE or PET scan to exclude direct heart injury due to tumor (when appropriate).
- Consult the Sponsor to determine whether subjects who continue the study will benefit the most.

Any AEs or SAEs caused by serum troponin increased should be reported as described in 9.2. For subjects with persistent heart injury during treatment with HQP1351, the Sponsor does not recommend special treatments based on the mechanism of action of HQP1351, but recommends routine supportive care and will handle with reference to the advice of internal medicine specialists and cardiologists.

#### 4.3.4 Treatments for patients who develop allergic reactions on or after Day 1

Potential allergic reactions or other inflammatory symptoms may be observed in subjects after HQP1351 is orally administered. Signs and symptoms of inflammation or allergy include: Fever, chills, chilliness, allergic reaction, rash, urticaria, measles, dizziness, hypotension, edema, bronchospasm, tachypnoea, flu-like symptoms, and other reactions.

Patients with symptoms and signs of allergy or similar reactions should be treated according to principles of the institution.

Prophylaxis should be given before each subsequent dose of treatment cycles to patients with allergy or similar reactions, including:

- 500 to 1,000 mg acetaminophen administered orally 30 minutes before dosing;
- 12.5 to 25 mg promethazine administered orally or intravenously 30 minutes before dosing;
- H1-receptor antagonists (e.g., loratadine) 30 minutes before dosing;

[figure not shown]

- Consider corticosteroids administered orally or intravenously according to the principles of the institution.
- The investigator will decide whether prophylactic administration of H1-receptor antagonists and/or corticosteroids is required. The investigator and the Sponsor will decide whether long-term prophylactic treatment is required in the cycles after allergic reactions are observed.

[figure not shown]

#### 4.3.5 Guidance for hypertension management during study drug administration

[figure not shown]

Refer to the Chinese Guidelines for the Prevention and Treatment of Hypertension for the use of antihypertensive drugs.

#### 4.4 End of Study and Efficacy and Safety Analysis

End of study means that all subjects have withdrawn from the study due to PD or other reasons. A final analysis of safety, efficacy and PK data will be performed at the end of study.

In this study, the recommended Phase II dose will be determined by the participating investigator and the sponsor based on safety, tolerability, PK, and available efficacy data.

The data cutoff date is the date on which each subject withdraws from the study due to PD or other reasons, and all data for all subjects acquired prior to this cutoff date will be analyzed.

#### 4.5 Premature Termination of Study

The sponsor can terminate the study at any time for any reason. If it is necessary to terminate the study, the patient should be timely notified to have end-of-treatment (EOT) visit as far as possible, and EOS assessment should be performed in subjects who withdraw prematurely. The investigator must be informed of other procedures to be followed, so as to ensure full consideration of the interests of subjects. The investigator will be responsible for notifying IRB and/or EC of premature termination of the trial.

[figure not shown]

## 5 Study Drug

### 5.1 CMC Introduction to HQP1351

#### 5.1.1 Study drug materials and dosage forms

HQP1351 for clinical trials is tablets, and each tablet contains 10 mg of HQP1351.

Chemical name: 3-[(1H-pyrazolo[3,4-b]pyridin-5-yl)ethynyl]-4-methyl-N-{4-[(4-methylpiperazin-1-yl)methyl]-3-(trifluoromethyl)phenyl}benzamide

Please refer to the Investigator's Brochure for additional information about the chemical and pharmaceutical properties of HQP1351.

#### 5.1.2 Packaging and labeling

The drug is stored in high density polyethylene (HDPE) bottles. Study drug labels will be in Chinese and comply with applicable legal requirements. The label should contain drug storage conditions, but does not contain information about the subject.

#### 5.1.3 Storage and handling

Clinical drugs must be stored in a secure place. See the label for details.

Drug manager must monitor the clinical drug storage area of the site to ensure that the temperature is within the appropriate storage temperature range specified in this protocol or the drug label attached to this protocol. Temperature monitoring document should be preserved.

#### 5.1.4 Usage

HQP1351 Tablets will be orally administered every two days (QOD), in a 28-day cycle. Subjects should take a prescribed dose of drug with meals and 250 ml water at the same time each day. During administration, subjects should maintain a normal diet.

If the study drug is not taken within 4 hours of the specified time, the dose will not be taken but be considered to be missed. This should be recorded in subject diary and reasons should be provided. If the study drug is vomited, it should not be re-administered. It should be considered a missed dose and recorded on the subject's diary with reasons indicated. If a subject delays administration or adjusts the dose for any reasons, the drug should be taken at the originally scheduled date and time.

### 5.2 Drug Management

On Day 1 of each cycle, subjects will be given the amount of study drug required for up to one cycle.

The investigator should designate a special person to receive, handle and store the study drug. The study drug should be stored in a safe place where only investigator and/or designated personnel who meets the condition can enter. The investigator should adequately manage all used and unused HQP1351, including the receipt record (quantity and conditions) of HQP1351

[figure not shown]

each shipment, inventory records at the study site, and individual dispensing record of patient. The receipt record should document the quantity received from the Sponsor. The dispensing form of study drug should document the quantity dispensed to patients, including drug batch number, dispensing date, subject number, initials of subject and initials of dispensing person. All unused HQP1351 dispensed to the subject must be returned to the investigator and recorded in the dispensing record (including the quantity of returned study drug, date, and receiving person).

Subjects must return all unused drugs and empty drug containers to the investigator. The CRA of the study will review all HQP1351 supply, use and returning records. Study sites should retain all HQP1351 and containers of used drugs until the CRA informs and instructs the site on how to dispose of and/or destroy all unused HQP1351. Any destruction of HQP1351 should be documented. If possible, after accounting, the sponsor can entrust the hospital to destroy the drugs according to standard procedure for destruction. The sponsor will count any unused investigational products and then entrust the hospital to destroy on the spot.

### **5.3 Treatment Compliance**

#### **5.3.1 Subject diary**

Subject diary card will be dispensed to each subject who takes the investigational drug at each visit and collected and reviewed at the next visit.

For a missed or vomited dose, subjects should be instructed not to take an additional dose in an attempt to make up for the missed or vomited dose. Subjects should be instructed to indicate on diary card that they didn't take the drug and state the reason(s).

#### **5.3.2 Tablet counting**

Remaining investigational drugs will be calculated. Subjects will be assessed for compliance with administration of the study drug. If the compliance is < 90%, the sponsor should be notified. For subjects with compliance less than 90%, the investigator and the sponsor will jointly decide whether the subjects continue participating in this study.

### **5.4 Randomization and Blinding**

The randomized part of this study will adopt a randomized and open-label design. The non-randomized part of this study will adopt a non-randomized and open-label study design.

In the randomized part, this study will use the Interactive Web Response System (IWRS) for central randomization. Each subject will be randomly assigned to a 30 mg, 40 mg, or 50 mg dose group. The randomization list used for central randomization will be generated by SAS 9.4 using block randomization and uploaded to the IWRS database. To ensure a balanced number of subjects across dose groups in each phase, the same randomization list will be used at all sites.

Since the randomized part of this study only involves randomization, it is a non-blind open-

[figure not shown]

label trial, and it is not necessary to blind the investigational products according to the generated randomization list.

## **5.5 Protocol Deviations**

Any deviation from the protocol procedure should be justified in the source documents. According to EC policy and procedure requirements, all serious deviations that may affect patient's safety, study drug use or the evaluation of safety, efficacy and tolerability parameters should be reported to the sponsor (or designated personnel) and EC of study site as soon as possible.

[figure not shown]

## **6 Prophylactic Treatment and Concomitant Medications/Treatments**

All concomitant medications, concomitant therapies, and concomitant clinical procedures during the period from the subject's signing of the written ICF to the visit 30 days after the last dose of HQP1351 should be recorded in the CRF.

### **6.1 Pre-treatment Drugs**

Information on all prior anticancer treatments (chemotherapy, radiotherapy, immunotherapy, biotherapy, etc.) received by the subject should be collected and recorded in the CRF.

Prophylactic medications should be avoided before Cycle 1. If an AE occurs in Cycle 1, prophylactic drugs may be administered in subsequent cycles.

